## Abstract

**Background**: Individuals with severe mental illness live, on average, up to 30 years less than the general population, with cardiovascular disease being the leading cause of death. Metabolic syndrome (MetS) plays a significant role in this, making it crucial to manage this issue in individuals with psychosis at the onset of the illness. The approach to managing this issue has evolved from a focus on calorie counting to a deeper understanding of hormone function, particularly the role of insulin resistance in MetS. Therefore, incorporating this perspective into mental health nursing consultations with individuals experiencing psychosis is of great interest. **Methods**: In accordance with the SPIRIT guidelines, an open randomized clinical trial is proposed, involving patients from a first-episode psychosis program. **Results**: The primary outcome will be significant weight loss (≥5%). Secondary outcomes will include changes in metabolic parameters, psychopathological status, quality of life, and physical activity. Participants will be assigned to two groups: one group will attend a series of six previously manualized nursing consultations, while the other will continue with their usual treatment. Results will be evaluated at six months and one year. **Conclusions**: This study will determine whether a mental health nursing consultation based on the carbohydrate–insulin model of obesity is effective in reducing weight and the risk of MetS in individuals with early-onset psychosis. This study was retrospectively registered on Clinical Trials—NCT06650943.

## 1. Introduction

The life expectancy of individuals with severe mental disorders is estimated to be 20 [1] to 30 [2] years shorter than that of the general population, with evidence suggesting that this disparity has widened in recent decades [3].

Cardiovascular and metabolic diseases are the main causes of death in this population group [4], and having a diagnosis of psychosis is considered a risk factor for the development of these diseases [5]. It is also a risk factor for death from cardiovascular or cerebrovascular events [6].

Metabolic syndrome (MetS), a common cause of cardiovascular and metabolic diseases, develops in one out of every three individuals experiencing psychosis, nearly doubling the odds compared to the general population [7,8]. MetS includes central obesity, increased fasting glucose, dyslipidemia, and hypertension, with insulin resistance playing a central role in various tissues of the body [9,10]. Different definitions have been proposed with similar criteria to diagnose MetS, which involve waist circumference, blood triglyceride levels, HDL cholesterol, fasting glucose, and systolic and diastolic blood pressure biomarkers [11,12,13].

In people who experience psychosis, one of the causes of MetS is the deregulation of glucose metabolism induced by antipsychotic treatment, especially second-generation antipsychotics [14]. In people who have experienced a first psychotic episode, the first year of treatment is crucial for weight gain and the establishment of metabolic alterations [15], with early insulin resistance being a predictor of weight gain and increased waist circumference [16], related to the alteration of hunger regulation [17]. With some exceptions such as Ziprasidone and Lurasidone, all antipsychotics cause significant weight variation, with a greater effect seen in the case of Clozapine and Olanzapine [18].

There is also evidence suggesting that the altered metabolic parameters may not only be due to antipsychotic treatment [19], but also involve other systems beyond the central nervous system in individuals with psychosis [20]. Poor dietary habits [21] or sedentary behavior, closely related to the negative symptoms of psychotic processes such as a lack of motivation or cognitive deterioration, have also been associated with MetS. Additionally, low economic income has been correlated with worse metabolic parameters [22].

For this reason, reference organizations such as the National Institute for Health and Care Excellence (NICE), in its guidelines for adult [23] and child [24] psychosis, and the International Physical Health in Youth (iphYs) working group [25], recommend monitoring these aspects in people who experience early-onset psychosis and implementing approaches to modify lifestyle habits in nutrition and physical activity.

The approach to metabolic disorders such as obesity and type 2 diabetes mellitus has been evolving in recent years [26]. The shift has been from a calorimetric perspective focused on calorie counting to an approach that emphasizes modifying the hormonal response triggered by various foods [27]. The carbohydrate–insulin model posits that the glycemic impact of nutrition triggers a hormonal response, particularly involving insulin, which in the long term affects weight variability and the development of metabolic and cardiovascular pathologies. Glucose spikes contribute to elevated insulin levels in the blood, hindering the use of fat as an energy source and promoting weight gain [28]. It has been observed that decreases in fasting insulin levels precede weight loss [29]. Moreover, the glycemic response to different meals could influence appetite and energy intake [30].

Given the evolving understanding of metabolic disorders, the role of healthcare professionals, including mental health nurses, needs to adapt to these changes. Mental health nurses, who serve as key health educators in individuals with mental health problems [31], have traditionally focused on providing nutritional education aimed at caloric balance, encouraging patients with psychosis to consume fewer calories and increase physical activity [32], or on identifying metabolic syndrome [33].

In studies employing a multidisciplinary approach, interventions that include an individualized follow-up [34] and a psychotherapeutic component have shown better results in managing MetS compared to purely educational group formats [35].

However, there is no evidence regarding whether nursing interventions that use a hormonal reference model are effective for weight management and reducing the risk of metabolic syndrome in individuals with recent onset psychosis.

Therefore, the aim of this study is to evaluate the effect of a nursing intervention based on the carbohydrate–insulin model on weight loss and the management of MetS risk in people with recent onset psychosis. Secondary aims include evaluating the effect of the intervention on (a) metabolic parameters related to MetS, (b) psychopathological state, (c) physical activity level, and (d) quality of life.

## 2. Methods

### 2.1. Design

This protocol is designed as an open-label, randomized clinical trial involving a group of patients in a first-episode psychosis (FEP) program, who will attend a series of nursing consultations focused on healthy habits aimed at addressing metabolic syndrome, in addition to their usual follow-up. The control group will consist of patients from the same program who will attend only routine nursing evaluation consultations.

The first author ([name]) will conduct the nursing consultations, based on a previously developed guide that structures and serves as a reference framework for the intervention.

This study was retrospectively registered on Clinical Trials—NCT06650943.

### 2.2. Setting

This intervention will take place within a hospital-based Early Intervention Program (EIP) for FEP patients at Basurto University Hospital (HUB) in Bilbao, Spain.

This EIP is a public program serving a total population of 347,000 people, with an annual attendance of 150 patients. Patients enter this program either through admission to the short-stay inpatient unit following a FEP, or by being treated in the Emergency Service for the same reason.

### 2.3. Participants

The inclusion criteria for the present study will include the following: (a) patients admitted to the EIP due to a (b) FEP within the last 5 years, (c) with a diagnosis of psychosis from the F2 spectrum or an affective disorder with psychotic symptoms as per the ICD-10 [36].

Exclusion criteria will include (a) cognitive inability to learn or a comorbid diagnosis of an intellectual disability that interferes with the study procedures, (b) a comorbid diagnosis of neurological pathology, (c) the presence of language or comprehension alterations that prevent accurate data collection, (d) being prescribed a hypoglycemic drug before or during the study, or (e) refusal to participate. No patients will be excluded based on their special dietary needs (e.g., celiac disease, veganism, special diets) or a diagnosis of MetS before the start of the intervention. The primary consideration will be the individual’s desire to improve their weight or metabolic status. A participant will be considered a drop-out if they miss 2 or more of the first 6 consultations, are admitted to the hospital due to psychotic relapse, and/or experience psychopathological decompensation characterized by a score of 5 or higher on items P1 (delusions), P2 (conceptual disorganization), P3 (hallucinatory behavior), P6 (suspiciousness, persecution), P7 (hostility), and/or G8 (uncooperativeness) on the Positive and Negative Symptoms Evaluation Scale (PANSS) [37], and/or exhibit clinically significant self-directed or outwardly aggressive behavior.

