### 2.4. Randomization and Treatment Allocation

Subjects will be selected during their psychiatry consultations following the stabilization of their pathology. If they meet the inclusion/exclusion criteria, they will be informed about the possibility of participating in the study, including its content and purpose. After being provided with an informed consent form and signing it, they will be randomly assigned to either the experimental or control group. Randomization will be conducted using a computer-generated random list. As participants are offered the opportunity to join the study, they will be assigned a number from the list in sequential order. The psychiatrist who refers the participants will not have access to the randomization list, ensuring allocation concealment. On the other hand, the psychiatrist responsible for administering the psychometric scales will be blinded to the intervention.

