### 2.8. Statistical Analysis

Categorical variables will be described as frequencies and percentages, while quantitative variables will be described as means and standard deviation (or medians and interquartile ranges where appropriate). Categorical variables will be compared using chi-square analysis or Fisher’s exact test, and quantitative variables will be compared using Student’s *t*-test, ANOVA, or the Mann–Whitney rank-sum test.

To compare changes in outcome variables between groups and over time, a multivariate mixed-effects model with repeated measures (linear or logit, depending on the characteristics of the variable) will be applied. Statistical significance will be assumed if the two-sided *p*-value is <0.05. The main analysis will assess the association between the study group and significant weight loss, defined as losing 5% of the original body weight.

To account for the potential effect of antipsychotics on weight and metabolic parameters, antipsychotics will be categorized as weight-increasing, weight-sparing, or as having non-conclusive effects. Sensitivity analyses will be conducted to examine the effect of each category on the outcomes. Categorization will be based on a review of previous evidence [42]. The use of weight-increasing antipsychotics in combination with weight-sparing antipsychotic use will be coded as weight-increasing antipsychotic use. The cumulative exposure of chlorpromazine-equivalent doses will then be calculated for each antipsychotic category in every patient [43].

Sensitivity analyses will also be conducted for each of the variables included in the previous section.

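### First-year and later patients are mixed in one sample, the main analysis credits only a loss of at least 5%, and time on treatment has no named place in the main model

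*Protocol article*

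**What the plan says.** All references are to the protocol article.

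- **Natural course (1. Introduction):** "the first year of treatment is crucial for weight gain and the establishment of metabolic alterations". The Abstract builds its rationale on this, "making it crucial to manage this issue in individuals with psychosis at the onset of the illness". No size of gain is given.
- **Entry (2.3. Participants):** "b) FEP within the last 5 years", with no weight, BMI or treatment-duration criterion. On weight it says only: "The primary consideration will be the individual’s desire to improve their weight or metabolic status".
- **Main analysis (2.8. Statistical Analysis):** the association between study group and "significant weight loss, defined as losing 5% of the original body weight". The Abstract also makes this threshold the primary outcome.
- **Model (2.8):** a multivariate mixed-effects model with repeated measures, linear or logit according to the variable. Its covariates are not listed.
- **Allocation (2.4. Randomization and Treatment Allocation):** "Randomization will be conducted using a computer-generated random list", with numbers taken in order. No strata are mentioned.
- **Time on treatment:** section 2.7 collects it at baseline. The last sentence of 2.8 promises sensitivity analyses for every variable in the preceding section, without giving their form.

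**The concern.** The same success rule is applied to patients whose expected untreated course differs. By the article's own account, someone early in treatment is followed through a period in which weight tends to rise. Someone several years on may be past it. For the first patient, staying at entry weight may be a real benefit, but it counts as a failure in either arm.

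Two things are at stake. The first is power: the more patients who would gain untreated, the fewer in either arm cross the 5%-loss line, and the harder the same benefit is to detect. The second is interpretation: from the main analysis alone, a null result would not separate an intervention that did nothing from one that held off gain. Time since treatment start is the collected variable that bears most directly on this, and it has no stated role in the main model.

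**Working it through.** **1. Reproduce the plan's sample size.** Section 2.9 gives a difference of 5 points, SD 7.5, power 80% and two-sided alpha 5%.

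Per arm: n = 2 × (1.96 + 0.842)² × 7.5² / 5² = 35.3, so 36 per arm (72 in all). The t-based version gives 36.3, so 37 per arm, or 74, which is the stated figure. It is a calculation for a difference in means. With 37 per arm the power for that test is about 81 to 82%.

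**2. Translate to the responder outcome.** Assume percent change is normal with SD 7.5 and the benefit is 5 points throughout. Let g be the mean untreated gain.

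- Control responders: Φ((−5 − g)/7.5)
- Intervention responders: Φ((−5 − g + 5)/7.5) = Φ(−g/7.5)

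The values of g, and the share f of patients who would gain, are assumptions; the article gives neither. The remaining share 1 − f is taken to have no gain. Power is for comparing two proportions with 37 per arm.

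| Scenario | Control | Intervention | Power |
|---|---|---|---|
| No background gain | 25.2% | 50.0% | 60% |
| Half would gain 5 points | 17.2% | 37.6% | 50% |
| Half would gain 10 points | 13.8% | 29.6% | 38% |
| All would gain 5 points | 9.1% | 25.2% | 45% |
| All would gain 10 points | 2.3% | 9.1% | 24% |

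The second row averages the no-gain and 5-point rates: (25.2 + 9.1)/2 = 17.2 and (50.0 + 25.2)/2 = 37.6. Over f = 0.25 to 0.75 and g = 3 to 10, power runs from 57% down to 29%.

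**3. Split the loss by cause.** From about 80% to 60% is due to dichotomising alone, with no gain at all (about 20 points). From 60% to 50% is due to the assumed stage mix in the second row (about 10 points).

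**4. The same mix with a continuous outcome.** With f = 0.5 and g = 5, the overall SD is √(7.5² + 0.5 × 0.5 × 5²) = √62.5 = 7.91, and power with 37 per arm is about 78%. A covariate that fully captured stage would bring the SD back to 7.5 and power to about 82%. Over the same range of f and g, unadjusted power for the mean difference is 81% to 67%.

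**5. Chance imbalance.** With 44 per arm and half in their first year, the between-arm difference in first-year share has SD √(2 × 0.25/44) = 0.107. At g = 5, a one-SD imbalance moves the mean difference by 0.107 × 5 ≈ 0.5 points, against a standard error of 7.5 × √(2/37) ≈ 1.7. Responder rates differ between stages by 16 points in controls (25.2 − 9.1) and 25 in the intervention arm (50.0 − 25.2). The shift in the responder difference is therefore about 2 points, against a standard error of about 10.

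**The case against.** The strongest reply is that the outcome fits the stated aim. The end of the Introduction defines that aim as weight loss and management of metabolic syndrome risk, and entry turns on a wish to improve weight or metabolic status. A reader might infer that prevention of gain is the real objective and that the primary outcome is therefore the wrong one. The document does not say so, and metabolic syndrome has its own secondary outcome. This reply stands: the primary outcome need not be replaced on this ground.

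It is also fair that prevented gain is not invisible throughout. The model in 2.8 may be linear, and weight is measured at every visit. But 2.8 names the binary association as the main analysis, so the headline result does not credit it.

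A reader might further infer that illness stage shrinks the benefit by about 35% (gain of 5 points) or 72% (gain of 10), since the responder difference falls from 24.8 to 16.1 or 6.8 percentage points. That holds only for risk differences and for groups in which everyone gains. On the logit scale named in 2.8, the odds ratios are about 3.0, 3.4 and 4.3, so the association does not shrink. What falls is power, because fewer patients respond.

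Nor does unstratified allocation bias the result. The test's error rate already allows for chance imbalance, and step 5 shows that the shift is small beside the standard error.

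Finally, this is a condensed article. Strata and covariates may be specified in a full protocol or analysis plan not shown, so it cannot be said that time on treatment is ignored. Recruitment after stabilisation (2.4) may also leave fewer patients still gaining, although the text refers to stabilisation of the illness, not of weight.

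**Conclusion.** The point holds as a matter of efficiency and interpretation, not of validity. The article itself identifies the first treatment year as the time of weight gain, enrols across five years, judges the main result on loss alone, and gives the relevant baseline variable only a general role.

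Under the plan's own effect and SD, with 37 per arm, a sample in which half would gain 5% has responder power of about 50%, against about 60% with no gain. The 10-point difference is what the stage mix adds; the larger fall, from about 80% to 60%, belongs to dichotomising. These figures rest on a normal model, a constant 5-point benefit, and an assumed gain and first-year share that the document does not supply.

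The document does not support reading this as a biased comparison or as an endpoint that contradicts the trial's aim.

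**What to change.** 1. Name time since start of treatment as a pre-specified baseline covariate in the main model, and fix its form (for example under one year against one year or more) before outcomes are examined. In the half-gaining-5% scenario about 20 of 74 participants respond ((17.2% + 37.6%)/2 × 74), so one extra term is affordable.
2. Add a secondary outcome of gain of at least 5% from entry weight at 6 and 12 months, and report continuous percent weight change beside it, so that prevented gain can be seen.

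**Cost:** one model term and derived variables from weights already scheduled in Table 1; no new data or visits. The downside is one more secondary comparison.

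Stratifying the list for participants still to be randomised, and showing results by stage, are optional. Changing the list part-way carries a procedural cost, and splitting about 74 evaluable participants leaves little power, so results by stage should be labelled exploratory.

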### 2.7. Instruments and Variables

Sociobiographic data will be collected, including sex, age, marital status, living arrangement, educational level, medical diagnosis, time since the beginning of treatment, substance use, antipsychotic type and dose, mood stabilizer use, and whether patients are assisted by a primary caregiver (considered as such if they assist in 4 of the first 6 consultations).

The primary outcome will be weight loss, with a reduction of 5% considered clinically significant [38]. Secondary outcomes will include the establishment or non-establishment of metabolic syndrome according to the International Diabetes Federation (IDF) criteria [12], which consist of abdominal obesity (abdominal circumference ≥ 94 cm in men and ≥80 cm in women) plus two of the following four factors: (i) elevated blood triglycerides (≥150 mg/dL or treatment for it); (ii) decreased HDL-c (<40 mg/dL in men and <50 mg/dL in women); (iii) high blood pressure (systolic blood pressure ≥ 130 mmHg and diastolic blood pressure ≥ 85 mmHg or antihypertensive treatment); and (iv) elevated fasting glucose (≥100 mg/dL or previous diagnosis of type 2 diabetes).

Anthropometric variables (weight, height, BMI, waist circumference) and vital signs (resting blood pressure) will be measured using calibrated equipment provided by the hospital.

Laboratory values (fasting blood glucose, glycosylated hemoglobin, triglycerides, HDL, HDL/LDL ratio, C-reactive protein) will be collected in accordance with hospital policy.

To measure psychopathology, the Positive and Negative Syndrome Scale (PANSS) will be used. This scale consists of 30 items divided into three subscales: positive, negative, and general. The positive subscale measures symptoms such as hallucinations and delusions, the negative subscale measures symptoms such as flat affect and lack of motivation, and the general subscale measures symptoms such as agitation and hostility [37].

Depressive symptoms will be assessed using the Hamilton Depression Rating Scale (HAM-D), which consists of 17 items, with higher scores indicating greater severity of symptoms [39].

The EuroQol-5D (EQ-5D) scale will be used to evaluate a person’s subjective well-being in relation to their health. The scale consists of five dimensions: mobility, self-care, usual activities, pain/discomfort, and anxiety/depression [40].

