### 2.10. Safety Assessments

Although no adverse effects are anticipated from the intervention, if they do occur, they will be recorded to the patients’ medical records and evaluated. In the event that risks are observed for participants or others, participation in the study will be suspended in those specific cases.

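### The drop-out rule is triggered by relapse and by PANSS scores, and PANSS is a secondary outcome; unless drop-outs are followed and analysed, the PANSS comparison is biased towards no difference and relapse is handled as attrition

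*Protocol article*

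**What the plan says.** Section 2.3 (Participants) lists the events that make a randomised participant a drop-out. The first is attendance: "A participant will be considered a drop-out if they miss 2 or more of the first 6 consultations". The others are clinical. Participants are drop-outs if they "are admitted to the hospital due to psychotic relapse", if they show "psychopathological decompensation characterized by a score of 5 or higher on items P1 (delusions), P2 (conceptual disorganization), P3 (hallucinatory behavior" (the list goes on to P6, P7 and G8), or if they show clinically significant aggressive behaviour. Any one of the six PANSS items is enough.

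The same construct is an outcome. The Abstract states: "Secondary outcomes will include changes in metabolic parameters, psychopathological status, quality of life, and physical activity". The aims in the Introduction include "b) psychopathological state, (c) physical activity level, and (d) quality of life". Section 2.7 names the instrument: "To measure psychopathology, the Positive and Negative Syndrome Scale (PANSS) will be used". HAM-D is the second psychopathology scale. Section 2.5 and Table 1 place the scales at the start and at about 6 and 12 months (weeks 24 and 48).

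Section 2.8 plans a mixed-effects repeated-measures model. Section 2.9 requires 74 participants and recruits 88 to allow for 20% dropout. Section 2.10 opens with "Although no adverse effects are anticipated from the intervention" and has any that occur entered in the medical record and evaluated.

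**The concern.** A value of the outcome scale after randomisation decides who counts as a drop-out. Section 2.4 recruits people once their illness has stabilised, so relapse or decompensation is the main way in which psychopathology can visibly worsen. Under the rule these events end a participant's status in the trial instead of counting as results.

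If drop-outs are not assessed further, three things follow. The upper end of the PANSS distribution is cut off in both arms, and cut more heavily in the arm that does worse, so the arms retain different survivors and the comparison is no longer as randomised. Later weight, quality-of-life and activity measurements go missing for the same people, and weight is the primary outcome. And a difference in relapse between arms would appear only as unequal attrition, not as a planned comparison.

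**Working it through.** **1. Does the plan treat drop-outs as lost?** Inputs from section 2.9: difference 5%, SD 7.5%, power 80%, two-sided alpha 5%. The standardised difference is 5/7.5 = 0.667. The t-based two-sample calculation gives 36.3, so 37 per arm and 74 in total, which matches the stated figure (the normal approximation gives 36 per arm, 72 in total). The step from 74 to 88 is the dropout allowance (74 x 1.2 = 88.8). An allowance of this kind is needed only if drop-outs do not contribute to the 74. The word drop-out therefore carries a consequence in the sample size, even though section 2.3 does not spell one out.

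**2. When can the rule bite?** Table 1 schedules PANSS only at weeks 1, 24 and 48.
- Triggered by the week 24 rating: that score exists, and only week 48 is at risk. If the score is kept, the later gap depends on an observed value, which the mixed model in section 2.8 can largely accommodate.
- Triggered by the week 48 rating: no later assessment is at risk, but the score itself must be kept.
- Relapse admission or decompensation between visits: no scheduled PANSS captures it, and every later assessment is at risk. The missing values then depend on unobserved severity, which the mixed model does not repair.

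The article does not say whether a triggering score is kept.

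**3. Size if those above the threshold are removed.** The documents give no relapse or threshold rate, so everything here is an assumption. Let severity on the trigger items and the PANSS outcome be standard normal with correlation r (0.5 to 0.9). Let the intervention shift both by d SD. Remove anyone whose severity exceeds t, with t chosen so that a proportion p of controls is removed (5%, 10%, 20%). With λ(x) = φ(x)/Φ(x):

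difference among those retained = d − r × [λ(t − d) − λ(t)]

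Example with p = 10%, d = 0.30, r = 0.9: t = 1.2816, λ(1.2816) = 0.195, λ(0.9816) = 0.2945. The retained difference is 0.30 − 0.9 × 0.0995 = 0.21 SD, a loss of about 30%.

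| True shift | Retained difference (SD), all p and r | Lost | Removed in shifted arm when p = 5 / 10 / 20% |
|---|---|---|---|
| 0.30 SD worse | 0.18 to 0.27 | 11 to 41% | 9 / 16 / 29% |
| 0.50 SD worse | 0.28 to 0.44 | 13 to 44% | 13 / 22 / 37% |
| 0.30 SD better | 0.20 to 0.28 | 8 to 34% | 3 / 6 / 13% |

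A simulation of the same model agrees to within about 0.003 SD. The bias is towards no difference for harm and for benefit alike.

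**4. What could a relapse comparison show?** Assume 10% against 20% with 44 per arm: 4.4 against 8.8 expected events. The pooled rate is 0.15. The standard errors are √(2 × 0.15 × 0.85/44) = 0.0761 under the null and √((0.09 + 0.16)/44) = 0.0754 under the alternative. Power = Φ[(0.10 − 1.96 × 0.0761)/0.0754], about 26%. Relapse can be reported descriptively but not tested with any confidence.

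**The case against.** The strongest reply is that section 2.3 only says who is considered a drop-out. It does not say that assessments stop, that data are deleted or that the analysis leaves these people out. Follow-up and handling of drop-outs are commonly set out in a full protocol or analysis plan, which is not shown. This stands as a limit: the bias is conditional on drop-outs not being followed. It does not remove the point, because the outcome-dependent rule is stated and section 2.9 counts drop-outs as lost.

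A reader might go further and infer that the trial cannot detect any effect or harm on psychopathology, or that its PANSS difference is near zero by construction. The documents do not support that. Only six of the 30 items trigger the rule, and only at 5 or above. The other 24 items, including the whole negative subscale, change below 5 on the trigger items, and HAM-D all remain measurable in those retained. Even with full removal above the threshold, more than half of the true difference survives in every scenario above.

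A reader might also multiply an assumed relapse difference by an assumed PANSS increment (for example 0.10 x 20 = 2.0 points) and conclude that this effect is removed entirely. That holds only if the whole effect runs through relapse, the arms do not differ otherwise, and every relapser's score is missing.

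Nor is the safety signal wholly hidden. The reasons for drop-out are defined and could be counted by arm, unequal removal would itself be visible, and section 2.10 provides for recording adverse effects. Weights taken before drop-out exist, since Table 1 schedules weight at every time point; only later values are at risk.

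**Conclusion.** The point holds in conditional form. The drop-out rule depends on a secondary outcome of the trial, and the sample size treats drop-outs as lost. If they are not followed and analysed, the PANSS comparison is biased towards no difference, by about 8 to 44% of the true effect. That range rests on assumed control-arm removal of 5 to 20%, true shifts of 0.3 to 0.5 SD, correlations of 0.5 to 0.9, and full loss above the threshold. Where triggering scores are kept, the loss would be smaller. A null PANSS result could then not be read as reassurance about psychopathology, and relapse would be attrition instead of a compared result. The effect on the primary weight outcome is loss of later data for the same people; its size cannot be estimated from the documents. The change should be made, although the main damage is to a secondary outcome and to safety reporting.

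**What to change.** In sections 2.3 and 2.8:
- Separate stopping the consultations from leaving the study. The clinical rule for stopping consultations can stay as written.
- Keep the PANSS score that triggers the rule, and use it in the analysis.
- Continue the week 24 and week 48 assessments (PANSS, HAM-D, weight, quality of life, activity) where feasible, unless the participant withdraws.
- Analyse all participants in the arm to which they were randomised.
- Report relapse admission and decompensation by arm, descriptively, given the low power.

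The cost is some wording and one extra table. The downside is that some assessments of unwell participants will be late or missing.
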